### Instruments

These are the main sources of information:

1) **Structured interview** that will be conducted in person at 13th, 20th and 32nd GW. The duration of the interviews will take approximately 35–40 min, which includes: the Athens Insomnia Scale (in English, AIS-8) [37], the Pittsburgh Sleep Quality Questionnaire [38], the Symptom Inventory in pregnancy [39, 40], short IPAQ [41], Adherence to the Mediterranean Diet, with Predimed questionnaire without wine [42]; 2) **Record of the average steps/day** of weeks 19 and 31 of gestation (information downloaded from the pedometer) and quantification of average hours of sleep at 19th and 31st GW (information downloaded from the Xiaomi Mi Band 2™ pedometer) (Fig. 1); 3) **Clinical history:** to collect the variables related to birth (tertiary outcome variables) and 4) Subsequent **telephone contact** if necessary (correction of missing data).

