### Arms and interventions

The three groups will receive information about the recommendation of physical activity during pregnancy, according to ACOG guidelines [19].

#### Arm 1

Intervention 1 (I1), maximum intervention: pedometer + goal + reminds (maximum intervention women receive information about the goal of steps/day to be reached: 10,000-11,000. They will receive messages on the mobile phone remembering the goal to achieve and a notification that the researching staff will proceed to collect the average count of steps/day of the week prior to 20th and 32nd GW. Women will get recommendations on physical activity during pregnancy.

#### Arm 2

Intervention 2 (I2), minimum intervention: use of pedometer watch from 12th to 32nd GW (10 weeks). They will not receive goal information nor reminds to collect information from the pedometer. Women will be given recommendations on physical activity during pregnancy.

#### Arm 3

No Intervention, control group: without pedometer. Women will receive recommendations on physical activity during pregnancy.

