### Outcome measures

Primary outcome measures in the three arms:

1) ***Prevalence of insomnia*** in third trimester of pregnancy (time frame: 32nd GW) will be evaluated with the Insomnia Athens Scale (IAS) [37], an eight-item scale that assesses the quantity and quality of sleep (first five items) and the diurnal repercussion of insomnia (daytime sleepiness, physical and mental functioning and well-being during the day). Each of the items scores from 0 to 3 (affectation of the item from light to severe). The total score ranges from 0 to 24 points, considering insomnia from a score equal to or greater than 6 points (Sensitivity = 93% and Specificity = 85%) or equal to or greater than 7 points (Sensitivity = 84% and Specificity = 90%).

2) ***Change in mean steps/day*** after intervention in the arms using pedometer register (time frame: 19th and 32nd GW).

Secondary outcome measures in the three arms (time frame: 12th, 19th and 32nd GW): ***Quality of sleep*** of pregnant women measure with the Pittsburgh Questionnaire (PSQI) [38], it assesses the quality of the individual’s sleep during the previous month. It consists of 19 items grouped into seven components: quality, latency, duration, efficiency and sleep disturbances, use of medication for sleep and diurnal dysfunction; each component is scored from 0 to 3, according to a Likert scale in which zero is the absence of the symptom and 3 is its maximum presence. This will result in a score that ranges from 0 to 21 points (the higher score, the worse sleep quality): a PSQI score of > 5 indicates poor sleep quality, with a diagnostic sensitivity of 89.6% and a specificity of 86.5%.

Other pre-specified outcome measures in the three arms:

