### Data analysis

A descriptive analysis of the variables collected in the study will be carried out. Measures of central tendency and dispersion will be calculated for the numerical variables and absolute and relative frequencies for the qualitative ones. The normality of the variables will be checked with the Kolmogorov-Smirnov test, in order to determine whether parametric or non-parametric tests will be carried out later. 95% confidence intervals (CI) will be obtained for both means and proportions.

For the contrast of the hypothesis of equality between the group of patients I1 and the group of patients I2, in terms of the number of daily steps and for each GW (19th and 31st), the Student t test will be used for independent samples or Mann-Whitney U, as appropriate. Subsequently, to assess whether there are differences between the groups with respect to the frequency of insomnia/quality of life for each trimester of pregnancy, the Pearson’s Chi-square test or Fisher’s exact test will be used when necessary.

On the other hand, to determine if differences are found between the quantitative variables (hours of sleep, quality of sleep) throughout the study period (first, second and third trimester) among the participants, the analysis of variance will be used for measurements repeated in the parametric case. In the case of having to use a non-parametric test, the Friedman test will be used. Subsequently, to assess the differences in the quality of life, for each of the groups, before starting the walking program and after finishing it (pre-post), the McNemar-Bowker test will be used.

For the contrast of the hypothesis of equality between the three groups of patients, regarding the weight gained during pregnancy (until 34 ^st^ GW), the weight of the newborn and the gestational week, an analysis of the variance or the test of Kruskall-Wallis will be used, as appropriate. In case of statistical significance, multiple comparisons will be obtained using the Student’s parametric test or the non-parametric Mann-Whitney U test applying Bonferroni correction.

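### Hours of sleep are to be tested over three trimesters, but their only stated source, the pedometer band, gives values at 19 and 31 GW and none in the control arm

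*Protocol article*

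**What the plan says.** **Analysis.** Data analysis names the variables, time levels and population as "quantitative variables (hours of sleep, quality of sleep) throughout the study period (first, second and third trimester) among the participants". The method is fixed in the same sentence: "the analysis of variance will be used for measurements repeated in the parametric case", with the Friedman test as the non-parametric alternative. The abstract likewise plans to analyse hours and quality of sleep in each trimester.

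**Source.** Instruments lists "quantification of average hours of sleep at 19th and 31st GW", with the source given as "information downloaded from the Xiaomi Mi Band 2™ pedometer". No other section says how hours of sleep are obtained.

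**Control arm.** Arms and interventions describes Arm 3 as "No Intervention, control group: without pedometer".

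**The other sleep instrument.** The PSQI is part of the structured interview held three times. Outcome measures lists it for all three arms, with components that include "quality, latency, duration, efficiency and sleep disturbances", each scored 0 to 3.

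**The concern.** A repeated-measures ANOVA or Friedman test over three trimesters needs a value in each trimester for each woman. The one source the article names for hours of sleep supplies two of the three, and only in the arms that wear the band. The article thus states both the variable's source and the levels at which it will be tested, and the two do not match.

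An analyst would have to improvise. One route is to use the device data that exist. The analysis then becomes a comparison of two time points in the pedometer arms, with no first-trimester value and no controls. The other is to substitute questionnaire duration. If that choice is made after the data have been seen, device or self-report could be picked by its result. Sleep is central to the trial's hypothesis, so the choice should be fixed in advance even for a supporting variable.

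**Working it through.** The plan states no figure to reproduce here. The check sets the planned levels beside the stated data and counts.

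**Step 1: weeks to trimesters.** Assumed cut-offs, which the article does not give: first trimester below 14 GW, second 14 to 27, third from 28.

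| Measurement | Weeks stated | Trimesters covered | Arms |
|---|---|---|---|
| Planned test of hours of sleep (Data analysis) | – | 1, 2, 3 | participants, no arm restriction |
| Device hours of sleep (Instruments) | 19, 31 | 2, 3 | I1, I2 |
| Device steps (abstract) | 12, 19, 31 | 1, 2, 3 | I1, I2 |
| PSQI (Instruments and abstract) | 13, 20, 32 | 1, 2, 3 | I1, I2, C |
| PSQI (Outcome measures) | 12, 19, 32 | 1, 2, 3 | I1, I2, C |

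The two sets of PSQI weeks differ slightly but map to the same trimesters.

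**Step 2: coverage of device hours.** Arm-by-trimester cells: 3 × 3 = 9. Cells with a stated device value: 2 arms × 2 times = 4. The first-trimester level is missing in every arm, and the control arm is missing at every level.

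**Step 3: women affected.** The block under Randomization of participants and concealment holds one control, four I1 and four I2. Expected controls: 265 × 1/9 = 29.4, about 29. The Sample size section implies 25 (265 − 120 − 120). Pedometer arms: 265 × 8/9 = 235.6, about 236. So about 29 women have no device hours, and about 236 have at most two stated values of the three planned.

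**Step 4: could the missing level exist unstated?** The abstract plans a pedometer reading at 12 GW in I1 and I2, but for steps only. If sleep were also downloaded then, coverage would be 2 arms × 3 times = 6 of 9 cells. Controls would still have none.

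**Step 5: does the test contrast arms?** As described, the ANOVA or Friedman test looks at change over time within women. The sentence states no arm factor. Complete data at three time points would therefore still give no comparison between arms from this test. That gap comes from the test itself; the missing control data are a second, separate obstacle for device hours.

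**The case against.** The strongest reply is that Data analysis does not say its hours of sleep are the device hours. The PSQI has a duration component and is given in all three arms at all three interviews, so a three-trimester series of sleep duration is planned for every woman. On this view the article has only left a source unstated, which a full protocol or analysis plan could settle.

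Part of this stands. A reader might infer that no woman has any three-trimester sleep-duration data, or that controls have no sleep information at all. The documents do not support that: the gap concerns device-recorded hours only. Nor do they exclude a device sleep value at 12 GW. It is unstated, and the assessment schedule in Fig. 1 is not available for checking.

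The reply does not remove the mismatch. The band is the only source the article names for hours of sleep. Data analysis lists hours separately from sleep quality, which is the PSQI outcome, and the PSQI duration item is described as a 0 to 3 score, not as hours. A later plan can choose between the sources, but it cannot create device data for women who have no device.

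It is also fair that hours of sleep is not among the primary, secondary or other pre-specified outcomes. That limits the weight of the point.

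**Conclusion.** The mismatch is in the text and is more than missing detail: the planned three-trimester test of hours of sleep cannot be run on the only source named for that variable. Device hours have 4 of 9 arm-by-trimester cells stated, with no first-trimester value and none for about 29 controls of 265. Device hours cannot be compared with control at any time.

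The severity is modest. The variable is not a listed outcome. The analysis of PSQI sleep quality, named in the same sentence, has data in all arms at all three times and is unaffected. It would also be wrong to blame the missing device data alone for the lack of a comparison with usual advice, because the within-woman test would not give one anyway.

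The conclusion assumes the trimester cut-offs above and takes the Instruments list at face value for device sleep. A sleep download at 12 GW would fill the first trimester in I1 and I2 but leave the control gap unchanged.

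**What to change.** In Data analysis:

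1. Name PSQI-reported sleep duration as the variable for the three-trimester analysis, since it is due in all arms at all three interviews.
2. Compare arms at 32 GW, adjusted for the first-interview value, because the within-woman time test gives no arm contrast.
3. Restrict device-recorded hours to I1 versus I2 at 19 and 31 GW. If a sleep download at 12 GW is intended, state it under Instruments.
4. State the scale. Use the reported hours if they are recorded; otherwise treat the 0 to 3 duration component as ordinal.

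The cost is wording only, since these data are already planned. There are drawbacks: PSQI duration is self-reported, a four-level component is much coarser than hours, and the comparison with control still rests on about 29 women. Step 2 is also a different analysis from the time test now written, so it should be fixed before the data are examined.

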### Baseline variables collected

Variables collected only in the first interview (13th GW) will be: *Sociodemographic variables* –age, number of previous children, number of children under 3 years, number of previous abortions, Spanish or foreign nationality, stable couple, level of studies, occupation of woman and partner (from these last two variables and taking into account the highest value, social class was calculated, with five categories in descending order I, II, III, IV and V, according to the Spanish Society of Epidemiology [43]); *Anthropometric variables:* height and pre-pregnancy weight.

### Variables collected in all interviews

- Diagnosis of pathologies in pregnancy: gestational diabetes, high blood pressure induced by pregnancy or preeclampsia and eclampsia.

- Drug use:

1) Consumption of **illegal drugs**: use of opiates, cocaine, cannabis and other drugs (specifying which) is recorded and if so, if the consumption is daily (number of times), weekly, monthly or occasional (number of days of consumption per week, per month or occasional and number of times per day of consumption); 2) Consumption of **medication and supplements** prescribed or not by a physician, reason and duration; 3) **Smoking habit**: 1. Active daily smoker; 2. Occasional smoker; 3. Recent former smoker (< 6 months); 4. Former smoker (> 6 months); 5. Never smoked [44]. *Active smoker*: average number of cigarettes per day; age of onset of consumption; *Former smoker:* How long ago did you stop smoking? Years or months. *Passive tobacco:* does your partner regularly smoke at home? If so: cigarettes/day; 4) **Alcohol:** number of drinks consumed daily, weekly, monthly or occasionally (wine or cava, beer with alcohol or cider, high-grade alcohol) [44] and 5) **Caffeine** consumption: number of cups (or bottles) that are consumed daily, weekly, monthly or occasionally of each of the following beverages: coffee, decaffeinated coffee, tea, cola, energy drinks and chocolates (milk or non-milk chocolate tablet).

*-* Physical activity*:* short IPAQ questionnaire [41], which includes the weekly frequency and minutes of completion of intense, moderate and walking physical activity. It allows the study sample to be classified into three categories according to their activity per week: low level or inactive (category I), moderate (category II) and active (category III).

*-* Diet*:* Adherence to the Mediterranean Diet pattern questionnaire, without wine [42]; 13-item questionnaire (olive oil, vegetables, fruits, red meat, chicken, fish, legumes, butter/margarine, carbonated drinks, industrial pastries, nuts, stir-fry) that are part of the Mediterranean diet. The higher the score obtained on the scale, the greater the adherence to the Mediterranean diet and is valued as acceptable adherence from 8 points.

### Outcome measures

Primary outcome measures in the three arms:

1) ***Prevalence of insomnia*** in third trimester of pregnancy (time frame: 32nd GW) will be evaluated with the Insomnia Athens Scale (IAS) [37], an eight-item scale that assesses the quantity and quality of sleep (first five items) and the diurnal repercussion of insomnia (daytime sleepiness, physical and mental functioning and well-being during the day). Each of the items scores from 0 to 3 (affectation of the item from light to severe). The total score ranges from 0 to 24 points, considering insomnia from a score equal to or greater than 6 points (Sensitivity = 93% and Specificity = 85%) or equal to or greater than 7 points (Sensitivity = 84% and Specificity = 90%).

2) ***Change in mean steps/day*** after intervention in the arms using pedometer register (time frame: 19th and 32nd GW).

Secondary outcome measures in the three arms (time frame: 12th, 19th and 32nd GW): ***Quality of sleep*** of pregnant women measure with the Pittsburgh Questionnaire (PSQI) [38], it assesses the quality of the individual’s sleep during the previous month. It consists of 19 items grouped into seven components: quality, latency, duration, efficiency and sleep disturbances, use of medication for sleep and diurnal dysfunction; each component is scored from 0 to 3, according to a Likert scale in which zero is the absence of the symptom and 3 is its maximum presence. This will result in a score that ranges from 0 to 21 points (the higher score, the worse sleep quality): a PSQI score of > 5 indicates poor sleep quality, with a diagnostic sensitivity of 89.6% and a specificity of 86.5%.

Other pre-specified outcome measures in the three arms:

1. ***Quality of life*** of women through pregnancy (time frame: 12th, 19th and 32nd GW), measure with the Pregnancy Symptom Inventory (PSI) [39, 40]: 41-item Likert scale developed from a group of experts and focus groups. It registers the range of symptoms that appears in the last month (Likert scale from 0 to 4: never, rarely, sometimes, often) and its impact on quality of life, by affecting the activities of daily life (scale Likert from 0 to 3: it does not limit me, it limits me a little, it limits me a lot). It has been adapted to Spanish pregnant women and is reliable (Kappa coefficient range = 0.6–0.9) [40]; 2. ***Women weight gain*** in kilograms (time frame: 12th and 32nd GW), measured with the hospital scale; 3. ***Weight of the new-born*** (time frame: delivery) collected from the clinical history of the women; 4. ***Gestational week at delivery*** (time frame: delivery) collected from the clinical history of the women.

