### Selection criteria for eligibility

Inclusion Criteria: 1) Pregnant women with a minimum of 18 and maximum of 49 years of age; 2) Low medical risk pregnancies that will be attending in the Unit of Obstetrics and Gynecology, in a public third level Maternity Hospital in Granada (Spain); 3) Sedentary women (< 5 days/week of moderate-vigorous physical activity at least > 30 min.; equivalent to < 7000 steps/day); 4) With mobile phone and e-mail; 5) Without intellectual deficits or difficulty to understand the language.

Exclusion Criteria: 1) Chronic disease: diabetes, high-pressure, cardiac or respiratory disease, liver or kidney disease or mobility problems; 2) Women with relative or absolute repose needed; 3) Active women (> 5 days/week of moderate-vigorous physical activity at least > 30 min.; equivalent to > 7000 steps/day); 3) Insomnia at beginning of pregnancy or having drugs for sleep problems.

The study sample will consist of women who, meeting the inclusion criteria, agree to participate, upon request for voluntary collaboration and signing of two documents: 1) Informed consent approved by the Provincial Ethics Committee of Granada and 2) Pedometer loan certificate.

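### Insomnia is an entry exclusion, yet its frequency is tested between arms in every trimester: the first-trimester test cannot inform on the intervention, and no clear arm comparison uses the AIS score

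*Protocol article*

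**What the plan says.** All references are to the protocol article.

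- **Selection criteria for eligibility** lists as an exclusion "Insomnia at beginning of pregnancy or having drugs for sleep problems". It gives no instrument, cut-off or visit.
- **Outcome measures** sets the first primary outcome as prevalence of insomnia "in third trimester of pregnancy (time frame: 32nd GW) will be evaluated with the Insomnia Athens Scale (IAS"). Two cut-offs are offered and neither is chosen. One is "considering insomnia from a score equal to or greater than 6 points", with a stated sensitivity of 93% and specificity of 85%. The other is a score of at least 7, with 84% and 90%.
- **Data analysis** plans Pearson's chi-square, or Fisher's exact test when needed, for "differences between the groups with respect to the frequency of insomnia/quality of life for each trimester of pregnancy". That wording includes the first trimester.
- **Instruments** places the AIS in an interview "that will be conducted in person at 13th, 20th and 32nd GW". Location and data collection puts the first interview at 12 weeks instead. The Abstract has women invited and randomised at 12 weeks, with the intervention running from 13 to 32 weeks.
- The last paragraph of **Data analysis** adds a mixed-effects logistic model of the variables that influence insomnia, and says that insomnia is treated there as a quantitative variable.

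**The concern.** The hypothesis in the Background is that the programme prevents insomnia from appearing by the third trimester. Two parts of the plan fit this badly.

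First, a between-arm insomnia test in the first trimester is made in women selected to be free of insomnia, at a visit where the intervention has had no time to act. A difference found there could only be chance or a fault in screening. Reported beside the later tests, it could be misread as an outcome result.

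Second, the 32-week outcome counts any woman at or above the cut-off on one interview, whatever her score at entry. A woman who entered just below the line is counted after a rise of a point or two, which ordinary score variation can produce. The planned test discards both the size of the change and the entry score. The control arm is small, since allocation in blocks of nine is 1:4:4, so there is little precision to give away.

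**Working it through.** **1. The first-trimester test.** There are two possible readings of the entry rule.

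- *Entry used the AIS at the outcome cut-off.* All arms have zero cases at the first interview. For 0 of 118 against 0 of 29 the expected counts are zero, so chi-square is undefined. Fisher's exact test returns p = 1.
- *Entry used history, self-report or another screen.* The AIS may then flag some women at the first interview. From the stated specificities, 15% (cut-off 6) or 10% (cut-off 7) of truly insomnia-free women would be flagged: 0.15 × 265 ≈ 40 or 0.10 × 265 ≈ 27 women. These would be baseline misclassification, not outcomes.

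Neither reading yields information on the intervention.

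**2. Women who cross the cut-off by noise alone.** The protocol gives no figure to reproduce.

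Inputs:
- 40% of women above the cut-off early in pregnancy (Background)
- retest correlation ρ of 0.7–0.9 (assumption; not in the document)
- no true change (assumption)
- same cut-off at entry and outcome (assumption)

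With a bivariate normal score and c = Φ⁻¹(0.60), P(second ≥ c | first < c) = 1 − Φ₂(c, c; ρ) / 0.60.

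| ρ | Φ₂ | Share crossing |
|---|---|---|
| 0.7 | 0.478 | 20.4% |
| 0.8 | 0.501 | 16.5% |
| 0.9 | 0.531 | 11.6% |

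If entry is AIS below 6 and the outcome is 7 or more, simulation of rounded scores with assumed SD 3–5 gives about 4–14%.

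A check that needs no ρ uses the stated specificities: false positives among truly insomnia-free women are 1 − 0.85 = 15% or 1 − 0.90 = 10%.

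**3. Effect on the contrast.** The Discussion aims at a 33% reduction from about 60%, that is 60% against 40%. The observed rate is p × sensitivity + (1 − p) × (1 − specificity).

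- Cut-off 6: 0.6 × 0.93 + 0.4 × 0.15 = 61.8%; 0.4 × 0.93 + 0.6 × 0.15 = 46.2%; difference 15.6 points.
- Cut-off 7: 0.6 × 0.84 + 0.4 × 0.10 = 54.4%; 0.4 × 0.84 + 0.6 × 0.10 = 39.6%; difference 14.8 points.

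A true 20-point difference shrinks to about 15. It is not reversed, and no difference is created where there is none.

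**4. Binary test against baseline-adjusted score.** Simulation, control against I1.

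- Arm sizes from the 1:4:4 blocks: 265/9 ≈ 29 and 265 × 4/9 ≈ 118.
- With 25% losses, the middle of the stated 20–30%: 29 × 0.75 ≈ 22 and 118 × 0.75 ≈ 88.
- Assumed: AIS SD 4, correlation 0.8, scores rounded to 0–24, entry below 6, and a worsening that would take unselected women from 40% to 60% at or above 6.
- Tests: chi-square on AIS ≥ 6 at 32 weeks; linear model of the 32-week AIS on arm and entry AIS. Two-sided 5%.

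| Women (C vs I1) | AIS benefit | Binary | Adjusted score |
|---|---|---|---|
| 29 vs 118 | 1.5 points | 48% | 81% |
| 29 vs 118 | 2 points | 72% | 96% |
| 22 vs 88 | 1.5 points | 40% | 67% |
| 22 vs 88 | 2 points | 59% | 90% |

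A separate run agreed within about two percentage points.

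**5. Does the entry exclusion cause the loss?** Without the exclusion, in the same setting at 29 vs 118, the binary test has about 32% and 50% power and the adjusted score about 82% and 97%. The exclusion therefore raises binary power. The gap comes from dichotomising.

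**The case against.** The strongest reply is that a single-visit prevalence at 32 weeks is exactly what the protocol declares, that noise common to randomised arms causes no bias, and that preferring a score to a dichotomy is a general preference and not an error. The first two statements stand, and the primary outcome should stay. The third stands in part: the dichotomy is legitimate as primary, but the AIS total is already collected at every interview and is left without a usable arm comparison.

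It can also be said that the mixed-effects model is already a quantitative analysis of insomnia. Its text calls for a logistic model of a quantity, and it is framed as a search for influencing variables. It is too contradictory to count as a pre-specified arm comparison of the score.

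Several stronger readings are tempting but not supported:

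- *Entry and outcome share one definition, so the first trimester has no cases by design.* The exclusion names no scale, and the outcome has two cut-offs. Zero cases follow only if entry used the same AIS cut-off.
- *Chi-square failing leaves no test at all.* The plan provides Fisher's exact test; it would simply return p = 1.
- *Some 12–20% of women will become cases by noise.* This rests on a retest correlation that the document does not give, on no true change, and on a shared cut-off.
- *Selecting women below the cut-off costs power.* In the simulation it does the opposite.

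**Conclusion.** The point holds in a limited form. The first-trimester between-arm insomnia test is uninformative about the intervention under any reading of the entry rule; this needs no assumption beyond the text. The entry definition is missing and the outcome cut-off is unresolved, so the two sections need to be reconciled.

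Noise crossing of the cut-off is plausible at roughly 4–20%, depending on the assumed correlation, spread and cut-offs. It weakens the contrast equally in all arms and does not favour the intervention.

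The gain from a baseline-adjusted AIS comparison is large in the illustrative setting, about 24 to 33 percentage points of power. The absolute values depend on the assumed SD, correlation and benefit.

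**What to change.** 1. **Data analysis:** limit the between-arm insomnia-frequency tests to 20 and 32 weeks. Use the first interview only as baseline.
2. **Selection criteria and Outcome measures:** state the same single AIS cut-off in both. Recruitment began in June 2019, so if a different screen was applied at entry, say which. Give one week for the first interview.
3. **Primary outcome:** keep AIS at or above the chosen cut-off at 32 weeks.
4. **Supportive analysis:** add one pre-specified between-arm comparison of the AIS total (0–24) at 32 weeks, in a linear model with arm and first-interview AIS. Let it replace the wording that describes a logistic model of insomnia as a quantity.

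A minimum rise in AIS as a further condition for new insomnia is not proposed, because the document offers no source for a threshold.

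Cost: wording only, with no new visit or measurement, and one more supportive result to report.

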### Sample size

First, we have carried out the theoretical calculation of the sample size for the definitive study (*n* = 265), based on the following premises: 1) Three study arms: *maximum intervention group*, pedometer + goal + recall (I1): minimum absolute reduction in the prevalence of low compliance with recommendations that are statistically significant to be detected, that it is 15% with respect to I1*; minimum intervention group*, pedometer (I2): minimum absolute reduction in the prevalence of low compliance with recommendations that are statistically significant to be detected, that is 30% with respect to C; and control group (C), with an estimated prevalence of low compliance with physical activity recommendations of 50% [12, 13]. 2) Alpha error: 5%; 3) Power of the study: 80%; 4) Comparison of I1 vs I2: from the previous premises, 120 women would be needed in each arm; Comparison of I1 vs C: from the previous premises, and taking as reference the 120 women of the I1 arm required for the previous comparison, 25 women in the C arm would be required.

A pilot of the previous design was carried out with 72 women not included in this study: 24 women in each arm of the study, interviewed twice (12th and 20th GW), during the months of February to May 2018. The recruitment period was 3 months. To select a total of 265 women, 1 year and 7 months would be required (considering holiday periods and Covid-19). We estimate 20–30% of losses in second and third interviews (due to neonatal loss or abandonment of the study).

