Finally, a bivariate mixed-effects logistic regression model will be carried out to determine which variables influence the greater frequency of insomnia, considering the latter quantitatively. To delimit the extent to which the associations that appear are explainable by the effect of the rest of the variables included in the study, a multivariate mixed-effects logistic regression model will be constructed. 95% confidence intervals (CI) will be obtained. All contrasts will be bilateral and statistical significance will be considered when the *p* value is ≤0.05. The data analysis will be carried out by intention to process and by protocol, using the Stata / SE v15.0 statistical package.

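### The primary insomnia endpoint has two cut-offs with none chosen, and neither the choice nor the second primary outcome is covered by any multiplicity rule, so the stated 5% alpha is not held

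*Protocol article*

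**What the plan says.** All of this is in the protocol article.

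- **Outcome measures, status.** Two outcomes stand under one heading, "Primary outcome measures in the three arms": prevalence of insomnia and change in mean steps per day. Neither is ranked above the other, and no rule says whether one or both must succeed.
- **Outcome measures, insomnia.** The time point is fixed: "in third trimester of pregnancy (time frame: 32nd GW) will be evaluated with the Insomnia Athens Scale (IAS"). The threshold is not. A score of at least 6 or at least 7 may define insomnia, each with its own accuracy: "Sensitivity = 93% and Specificity = 85%) or equal to or greater than 7 points (Sensitivity = 84% and Specificity = 90"%).
- **Data analysis, insomnia.** Chi-square or Fisher tests compare the groups "with respect to the frequency of insomnia/quality of life for each trimester of pregnancy".
- **Data analysis, steps.** I1 and I2 are compared separately at the 19th and 31st GW. (Outcome measures gives the 19th and 32nd.)
- **Data analysis, multiplicity.** The only correction covers follow-up comparisons of weight gain, newborn weight and gestational week: "non-parametric Mann-Whitney U test applying Bonferroni correction".
- **Data analysis, significance.** "All contrasts will be bilateral and statistical significance will be considered when the *p* value is ≤0.05".
- **Sample size.** "2) Alpha error: 5%; 3) Power of the study: 80"%.

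**The concern.** A binary primary endpoint needs one threshold. With two on offer, the analyst can run both and report the one that reaches significance, and nothing in the text forbids it. The same freedom exists over which primary outcome carries the conclusion, which step week counts, and whether insomnia is judged across three arms or by pairs. The plan does use a multiplicity correction, but only for outcomes it ranks below the primary and secondary ones.

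At stake is whether a reported p ≤ 0.05 for the primary outcome means what the sample-size section says it means. Participants cannot be blinded, and AIS is self-reported at interview, so a pre-fixed primary test is one of the few protections available.

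**Working it through.** **Inputs from the protocol article**
- Two-sided alpha 0.05 for every contrast.
- Arms of 120 (I1), 120 (I2) and 25 (C): 120 + 120 + 25 = 265. The 4:4:1 blocks would instead give 265 × 4/9 = 117.8, 117.8 and 265/9 = 29.4. The insomnia results barely change.
- Late-pregnancy insomnia of about 60% (Discussion).
- Cut-offs of at least 6 and at least 7; step tests at two weeks.

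**Assumptions (not in the document)**
- Prevalence at ≥6 / ≥7 of 60/50%, 60/55% or 45/37%.
- Correlation between visits of 0.3–0.7 for AIS and 0.4–0.8 for steps; AIS with steps −0.2.

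**The plan's own figure.** The document gives no family-wise error rate; its figure is alpha = 5%. One cut-off at 32 GW with one three-arm chi-square gives 4.9–5.3% in simulation under no effect, so a single fixed test does deliver the stated alpha.

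**Bound for independent tests.** Family-wise error = 1 − (1 − 0.05)^k.
- k = 2 (one insomnia test, one step test): 1 − 0.95² = 9.75%.
- k = 4 (two cut-offs, two step weeks): 1 − 0.95⁴ = 18.5%.

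The two cut-offs overlap heavily and the step weeks are correlated, so the true figure for k = 4 is lower and has to be simulated.

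**Simulation under no effect** (20,000 trials per scenario; false positive = any p ≤ 0.05 in the family; range over the assumptions)

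| Family of tests | False-positive rate |
|---|---|
| One cut-off, 32 GW, three-arm test | 4.9–5.3% |
| Either cut-off, 32 GW, three-arm test | 7.0–8.1% |
| One cut-off, 32 GW, all pairwise arm tests | 11.4–12.3% |
| Either cut-off, 32 GW, all pairwise arm tests | 16.1–17.9% |
| Either cut-off (three-arm) plus steps at both weeks: primaries as listed | 14.4–16.3% |
| Either cut-off (pairwise) plus steps at both weeks | 22.9–25.0% |

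The first four rows concern the insomnia claim alone. The last two assume that any one success counts.

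**Does a repair restore 5%?** One cut-off with pairwise tests run only after a significant three-arm test gives 4.8–5.0%. A single pre-named contrast is one test at 5%. Two primaries, one test each at 0.025, give 1 − 0.975² = 4.9% if independent.

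**Cut-offs compared on the document's own figures.** Youden index = sensitivity + specificity − 1. For ≥6: 0.93 + 0.85 − 1 = 0.78. For ≥7: 0.84 + 0.90 − 1 = 0.74.

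**Power cost of gating.** Reading the Discussion's reductions as relative to 60%: I1 60 × (1 − 0.33) ≈ 40%, I2 60 × (1 − 0.166) ≈ 50%, C 60%. With 118/118/29, power for I1 vs C is about 50% tested directly and about 41–42% behind the three-arm gate. With 25% loss it is about 40–41% and 30–31%.

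**The case against.** The case for leaving the plan alone has several parts.

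- **Multiplicity rules often sit in a statistical analysis plan that is not shown.** This is fair for a missing hierarchy taken alone. It does not cover a primary endpoint that the article itself defines in two ways, a blanket p ≤ 0.05 rule, or a correction the article assigns explicitly to other outcomes.
- **Evaluators and analysts work without knowledge of allocation** (Randomization section). This helps, but it does not settle which cut-off is the primary one.
- **The inflation from the cut-off alone is modest.** This stands: 7–8%, not a multiple of 5%, if one three-arm test is used.

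A reader might also infer more than the document supports:

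- *That the error rate simply is 16–25%.* This needs an either/or success rule, which the document does not state. If both primaries had to succeed, having two would not inflate error. The top of that range also needs unadjusted pairwise insomnia tests. Data analysis speaks only of differences between groups, although Sample size and the Discussion do frame the aims as contrasts between pairs of arms.
- *That primary insomnia can be won at several visits.* It cannot: it is fixed at 32 GW. The per-trimester tests do not turn 20 GW into a primary route. Only steps has two primary weeks.
- *That a step difference could win the insomnia claim.* A difference between I1 and I2 in steps says nothing directly about insomnia.
- *That the first-trimester insomnia test is empty by design.* The exclusion of early insomnia names no instrument or cut-off, so this is not established.

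**Conclusion.** The concern holds in limited form. The cut-off for the primary endpoint is left open, two primaries are unranked, one of them is tested at two weeks, and no adjustment reaches any of this. The plan as written therefore does not guarantee its stated 5%.

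For the insomnia claim alone the rate is about 7–8% with a three-arm test and about 16–18% with unadjusted pairwise tests. For the primary tests as listed it is about 14–16%, and up to about 25% with pairwise arm tests added, in both cases only if any one success may count.

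The direction does not depend on the assumptions. The exact sizes rest on the assumed gap between the cut-offs and the assumed correlations. The point should be settled before analysis; it does not undermine the design.

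**What to change.** Before any outcome is examined by arm, record the following in a dated amendment or analysis plan:

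1. **One AIS cut-off** for the 32 GW primary analysis, with the other as a sensitivity analysis. On the document's figures ≥6 has the slightly higher Youden index, but that index weights sensitivity and specificity equally; either cut-off is acceptable if fixed in advance.
2. **One primary insomnia test**: either a pre-named I1 vs control contrast at 5%, or the three-arm chi-square at 5% with pairwise tests only if it is significant.
3. **One named week for steps**, with the 31st/32nd GW wording reconciled, tested either after insomnia in fixed order or with Holm across the two primaries.
4. **Label as supportive** the 20 GW insomnia test and the step test at the other week.

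This changes analysis wording only; sample size, visits and eligibility stay as they are. Recruitment began in June 2019, so the record should show that the choice preceded any look at outcomes by arm.

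The costs are real. Lower-ranked comparisons cannot be claimed if the first test fails. The three-arm gate takes roughly 8–10 percentage points of power from I1 vs control in the scenario above. If that contrast is the main interest, naming it directly avoids the loss.
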